## Abstract

**Background:**

Depression is one of the most prevalent and disabling non-motor symptoms in Parkinson’s disease (PD), forming a bidirectional relationship with motor dysfunction that worsens quality of life. Pharmacological treatments exhibit limited and inconsistent efficacy, and may lead to adverse interactions. Acupuncture may improve both depressive and motor symptoms by regulating the neuro–immune–endocrine network, but high-quality evidence remains insufficient.

**Objective:**

This study aims to evaluate the efficacy and safety of acupuncture as an adjunctive therapy for depression in PD and to explore potential biological correlates of clinical changes using predefined serum biomarkers.

**Methods:**

In this single-center, evaluator-blinded, randomized controlled trial, 88 patients with PD and comorbid depression will be randomly assigned to an acupuncture group or a waitlist control group. The primary outcome is the change in the Montgomery–Asberg Depression Rating Scale (MADRS) score. Secondary outcomes include motor function, anxiety, sleep quality, and overall quality of life. Exploratory analyses will assess serum inflammatory cytokines, brain-derived neurotrophic factor (BDNF), and kynurenine/tryptophan (KYN/TRP) ratio.

**Expected results:**

We hypothesize that adjunctive acupuncture may improve depressive and motor symptoms compared with the control. Exploratory analyses will examine whether clinical changes are associated with changes in relevant biomarkers.

**Conclusion:**

This study will provide rigorous evidence for acupuncture as an adjunctive therapy, offering a non-pharmacological strategy to optimize the comprehensive management of PD and disrupt the bidirectional emotion–motor interplay.

**Clinical trial registration:**

https://www.chictr.org.cn/, identifier ChiCTR2500113443.

## Introduction

1

Depression is among the most challenging comorbidities in the management of Parkinson’s disease (PD) (1). As the most common non-motor symptom, it imposes a considerable epidemiological burden. Approximately 38% of patients with PD develop depression (Parkinson’s disease with depression, PD-D) (2), with a prevalence nearly four times that of the general population and up to ten times higher among individuals over 50 years of age.

Notably, depressive symptoms may precede motor manifestations and establish a maladaptive bidirectional relationship with motor impairment (3). Depression exacerbates bradykinesia, rigidity, and postural instability (4), while motor decline is often linked to the onset or worsening of depressive symptoms (5). This mutually reinforcing pathological process independently predicts disability progression, accelerates functional decline and deterioration in quality of life, and substantially increases the risk of dementia, mortality, and suicide (6, 7).

Therefore, depression in PD is not merely a frequent emotional comorbidity but a pivotal driver of overall disease progression and adverse outcomes. It also places an additional burden on families and healthcare systems (8).

However, current pharmacological and psychological interventions face significant limitations in clinical practice. Although selective serotonin reuptake inhibitors (SSRIs) are considered first-line therapy, evidence for their efficacy in PD remains inconclusive (9). Most trials have been limited by small sample sizes and inconsistent findings, and treatment responses show considerable interindividual variability (10).

Long-term polypharmacy further complicates management. For example, combining SSRIs with monoamine oxidase B inhibitors may trigger serotonin syndrome, while medications such as levodopa can induce or worsen non-motor symptoms, including anxiety and insomnia (11). More importantly, most pharmacological agents target only a single symptom domain, limiting their ability to simultaneously improve both motor and affective symptoms (12). Consequently, patient adherence is often poor, and treatment satisfaction remains low.

Psychological interventions, including cognitive behavioral therapy, are recommended in current guidelines for the management of depression in Parkinson’s disease and have demonstrated efficacy in selected patient populations (13). In routine clinical practice, however, their implementation and uptake may be influenced by contextual factors such as therapist availability, cognitive status, treatment intensity, and patient preference. In particular, some patients with PD-related depression present with prominent somatic symptoms or express a preference for interventions targeting physiological regulation, which may affect engagement with purely psychotherapeutic approaches. In this context, there remains a need to explore additional non-pharmacological options that can be used alongside standard care.

The pathogenesis of depression in PD involves multiple pathological pathways shared by both affective and motor symptoms. In addition to dopaminergic dysfunction, impairments in the serotonin and norepinephrine systems play critical roles in emotional regulation and motor control (3). Chronic neuroinflammation, hyperactivation of the hypothalamic-pituitary-adrenal (HPA) axis, and reduced levels of brain-derived neurotrophic factor (BDNF) are closely linked not only to the onset of depression but also to the acceleration of neurodegeneration (9).

Furthermore, disturbances in the kynurenine/tryptophan (KYN/TRP) metabolic pathway decrease the availability of serotonin precursors, facilitating depressive symptoms (14). At the same time, this imbalance promotes the accumulation of neurotoxic metabolites, such as quinolinic acid, which exacerbates dopaminergic neuronal injury and worsens motor dysfunction (15). Together, these findings indicate that depression and motor impairment in PD share convergent pathological mechanisms mediated through neuro–immune–endocrine networks, providing a solid theoretical foundation for integrated therapeutic approaches.

Acupuncture, a safe and widely accepted non-pharmacological therapy, has shown promising potential in the comprehensive management of depression in PD. Evidence from previous studies suggests that acupuncture may influence multiple neurobiological processes relevant to PD-related depression, including neurotransmitter regulation, inflammatory modulation, neurotrophic support, and tryptophan metabolism (16). These mechanisms closely align with the core pathological pathways of PD-related depression, indicating that acupuncture may provide concurrent benefits for both depressive and motor symptoms (17).

However, most existing evidence comes from exploratory studies with small sample sizes, single-center designs, and considerable methodological heterogeneity. As a result, high-quality data that systematically integrate clinical outcomes with objective biological markers remain scarce (18).

Despite these encouraging findings, several key uncertainties remain. Prior studies are often limited by exploratory designs, restricting the precision and interpretability of effect estimates. In addition, most research has relied predominantly on symptom-based outcomes, with limited integration of objective biological markers, leaving it unclear whether observed clinical improvements reflect modulation of underlying neurobiological pathways. Finally, although depression and motor dysfunction in Parkinson’s disease interact bidirectionally, it remains uncertain whether acupuncture is associated with concurrent improvements across both affective and motor domains within the same clinical framework.

Accordingly, we designed a prospective, evaluator-blinded randomized controlled trial to evaluate the efficacy and safety of acupuncture as an adjunct to stable standard pharmacotherapy in patients with Parkinson’s disease and comorbid depression. This study integrates serum biomarkers—including inflammatory cytokines, brain-derived neurotrophic factor (BDNF), and the kynurenine/tryptophan (KYN/TRP) ratio—with clinical outcome measures, enabling an exploratory assessment of whether acupuncture is associated with coordinated improvements in depressive and motor symptoms through shared neuro–immune–endocrine pathways.

## Methods and analysis

2

### Study design

2.1

This study will be a single-center, prospective, evaluator- and statistician-blinded, two-arm, parallel-group randomized controlled trial (RCT) that will be conducted at the First Affiliated Hospital of Guangzhou University of Chinese Medicine. We will recruit 88 patients with PD-D, who will be randomly assigned in a 1:1 ratio to either the acupuncture treatment group or the waitlist control group.

All participants will maintain their stable, standard medication regimen throughout the study. A waitlist control design will be used to assess the add-on benefit of acupuncture. For ethical reasons, participants in the control group will be offered compensatory acupuncture treatment after the 6-week control period.

The study flow is illustrated in **Figure 1**, outlining the entire process from screening to follow-up. The schedule for all interventions, assessments, and follow-up visits is summarized in **Table 1**. Patients and the public were not involved in the design or conduct of this trial; however, results will be disseminated to participants in plain language after study completion.

**Figure 1 f1:**
[figure not shown]
Study flowchart.

**Table 1 T1:** Schedule of enrollment, interventions, and assessments.

Study phase	Assessment content	Screening (W-1 ~ W0)	Baseline (W0)	Primary endpoint (W6)	Follow-up (W8)	Follow-up (W12)	Follow-up (W24)
Enrolment	Eligibility Screening & Informed Consent	✓					
	Demographic & Medical History Information	✓					
	Randomization		✓				
Assessment	MADRS	✓	✓	✓	✓	✓	✓
	HADS		✓	✓	✓	✓	✓
	MDS-UPDRS-III		✓	✓	✓	✓	✓
	PDQ-39		✓	✓	✓	✓	✓
	PSQI		✓	✓	✓	✓	✓
	PGIC			✓	✓	✓	✓
	ZBI		✓	✓	✓	✓	✓
	Acupuncture Expectancy Scale		✓				
	Blood Samples		✓	✓			
Safety	C-SSRS	✓	✓	✓	✓	✓	✓
	Vital Signs¹		✓	✓			
	Adverse Events/Concomitant Medications	✓	✓	✓	✓	✓	✓

¹Vital signs will be assessed at baseline (W0) and at the primary endpoint (W6).

### Participants

2.2

We will consecutively recruit participants from July 2025 to July 2026 from the acupuncture outpatient clinics and inpatient wards of the First Affiliated Hospital of Guangzhou University of Chinese Medicine. All candidates must be evaluated by a specialist physician, meet the diagnostic criteria for PD-D, and have been on a stable anti-Parkinson’s medication regimen (unchanged dosage and type) for at least 4 weeks before enrollment.

Recruitment will be conducted through multiple channels, including referrals from the outpatient and inpatient departments of Acupuncture, Neurology, and Rehabilitation. On-site promotional materials (e.g., posters, electronic displays) and announcements on the hospital’s official website and WeChat account will also be used.

During the screening phase, trained researchers will systematically collect demographic data (gender, age, education level), medical history (age of onset, disease duration, past and current treatments), and document motor and non-motor symptom characteristics. A trained researcher will explain the study protocol and potential risks to each candidate in a quiet, private setting. Written informed consent will be obtained from all participants after ensuring they fully understand the study and voluntarily agree to participate.

### Diagnostic criteria

2.3

Currently, there are no internationally accepted diagnostic criteria specifically for depression in PD-D. Therefore, the diagnosis in this study will be based on the following established standards:

Diagnosis of PD: Participants must meet the 2015 clinical diagnostic criteria set by the Movement Disorders Society (MDS) (19).

Diagnosis of Depressive Disorder: Participants must meet the criteria for depressive disorders as outlined in the Diagnostic and Statistical Manual of Mental Disorders, Fifth Edition (DSM-5), published by the American Psychiatric Association.

All diagnoses will be independently made by a qualified neurologist or psychiatrist.

#### Inclusion criteria

2.3.1

Participants meeting the following criteria will be included:

Meet the 2015 MDS clinical diagnostic criteria for PD and the DSM-5 diagnostic criteria for depressive disorder (19).Aged 40–80 years, inclusive, of either gender.Hoehn–Yahr stage 1–3 (20).A baseline MADRS total score between 7 and 34, inclusive, indicating mild to moderate depressive symptoms.Have received antiparkinsonian medication for ≥6 months and have been on a stable dosage for ≥4 weeks prior to enrollment.Stable vital signs, no impaired consciousness, and the ability to communicate normally and complete all study assessments.Voluntarily agree to participate and provide written informed consent.

#### Exclusion criteria

2.3.2

Participants will be excluded if they meet any of the following criteria:

Concurrent severe psychiatric or neurological disorders (e.g., schizophrenia, bipolar disorder, severe cerebrovascular disease).Initiation, discontinuation, or adjustment of antidepressant medications within 4 weeks prior to enrollment; or receipt of any specific intervention for depression (e.g., acupuncture, electroacupuncture, rTMS, psychotherapy) within 4 weeks prior to screening.Concurrent severe systemic diseases (e.g., severe cardiovascular disease, hepatic or renal failure, malignancy), or any condition that may significantly interfere with inflammatory marker assessment (e.g., active infection, regular use of NSAIDs).Significant suicide risk or a recent history of suicidal behavior, as determined by the Columbia-Suicide Severity Rating Scale (C-SSRS).Pregnant or lactating women, or individuals planning pregnancy during the trial period.Known contraindications to acupuncture (e.g., severe needle phobia, history of acupuncture-related syncope, bleeding tendencies, localized infection, or severe arrhythmia).Presence of an implanted deep-brain stimulation (DBS) device.History of alcohol or substance abuse within the last 3 months.

#### Dropout and discontinuation criteria

2.3.3

Participants will be withdrawn from the study if any of the following criteria are met. The reason for withdrawal will be documented in detail and included in the final analysis. Withdrawal will not affect access to routine clinical care.

Occurrence of a serious adverse event (SAE), or significant worsening of psychiatric symptoms, defined as either (1) an increase in the MADRS total score of more than 50% compared with baseline, or (2) the emergence of clinically significant suicide risk as assessed by the Columbia–Suicide Severity Rating Scale (C-SSRS), or the development of a serious concomitant illness, if the investigator deems continuation inappropriate.

Clinically significant motor worsening is additionally defined as safety-driven deterioration requiring urgent escalation of antiparkinsonian therapy (e.g., new initiation or a clinically necessary substantial dose increase), hospitalization for motor complications, or recurrent injurious falls requiring medical attention; when feasible, a clinically meaningful increase in the MDS-UPDRS III score will be recorded to support documentation.

Inability to continue due to poor adherence, frequent missed visits, or loss to follow-up (e.g., failure to complete ≥2 consecutive follow-up visits).

Any other circumstance deemed unsuitable for continued participation based on a comprehensive assessment by the study team.

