#### Waitlist control group

2.7.2

Participants in the waitlist control group will continue their stable, standard medication regimen for the 6-week study period. They will not receive acupuncture or any other study-specific interventions during this time. For ethical reasons, participants in the control group will be offered compensatory acupuncture treatment (using the same protocol as the acupuncture group) after the 6-week intervention period concludes.

To ensure comparability, all participants in both groups must maintain a stable antiparkinsonian medication regimen throughout the study. If any dose adjustments are necessary, they will be assessed by the investigator, documented in the CRF, and converted to the levodopa equivalent dose (LED) (26). No new systemic interventions that could potentially affect depressive symptoms will be permitted during the study. All changes in concomitant medications will be fully documented.

The use and dosage of antidepressant medications will be kept stable whenever possible throughout the 6-week controlled period. “Stable” is defined as no initiation, discontinuation, or dose change within 4 weeks prior to enrollment. During the trial, clinically indicated adjustments will be permitted for safety reasons or symptom worsening. All changes (type, dose, timing, and reason) will be documented and accounted for in the ITT analysis, with sensitivity analyses performed to assess robustness.

To monitor potential contamination during the waitlist period, at each assessment visit participants will be asked using a standardized checklist whether they have received any acupuncture or other non-study interventions for mood or motor symptoms (including acupuncture, electroacupuncture, moxibustion, rTMS, or psychotherapy) since the last visit. Any such use will be recorded as a protocol deviation (type, frequency, timing, and provider) and considered in the per-protocol and sensitivity analyses.

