### Statistical analysis methods

2.10

The ITT population will include all randomized participants analyzed according to the group to which they were assigned, regardless of adherence. Missing outcome data will be handled under the MMRM framework. A per-protocol (PP) analysis will also be conducted as a sensitivity analysis, excluding major protocol deviations. All statistical analyses will be performed using SPSS Statistics version 26.0 (IBM Corp., Armonk, NY, USA).

Continuous variables will be described as mean ± standard deviation (SD) or median (interquartile range, IQR), while categorical variables will be presented as frequencies and percentages. Baseline characteristics will be compared between groups using appropriate parametric or non-parametric tests.

The primary outcome (change in MADRS score) will be analyzed using a mixed-effects model for repeated measures (MMRM). The model’s fixed effects will include group, time, and the group-by-time interaction. Baseline MADRS score, the stratification factors (baseline severity and antidepressant use), and the Acupuncture Expectancy Scale score will be included as covariates (37). To assess the robustness of the primary findings and to address potential dilution effects associated with very mild depressive symptoms, a prespecified sensitivity analysis will be conducted excluding participants with baseline MADRS scores in the very mild range (e.g., MADRS < 10). The primary analysis model will be re-run in this restricted sample.

Missing values will be assumed to be missing at random (MAR) within the MMRM framework. Sensitivity analyses will be conducted using multiple imputation and pattern-mixture models. Key secondary outcomes (treatment response and remission rates) will be analyzed using chi-square or Fisher’s exact tests. Logistic regression will be used to adjust these outcomes for covariates, and results will be reported as odds ratios (ORs) with 95% confidence intervals (CIs).

Other continuous outcomes (e.g., MDS-UPDRS III, HADS, PDQ-39, PSQI) will be analyzed using ANCOVA or MMRM. Exploratory mechanistic biomarkers will be analyzed using ANCOVA with a false discovery rate (FDR) correction. These exploratory analyses are intended for hypothesis generation only.

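### Section 2.3.3 withdraws participants from the study without separating the end of treatment from the end of assessment, so anyone withdrawn before Week 6 is not assured a post-baseline MADRS

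*Protocol article*

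**What the plan says.** Section 2.3.3 (Dropout and discontinuation criteria) opens with the rule "Participants will be withdrawn from the study if any of the following criteria are met". The grounds are:

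- a serious adverse event, marked psychiatric worsening (a MADRS rise above 50%, or suicide risk on the C-SSRS) or serious illness, qualified by "if the investigator deems continuation inappropriate";
- motor worsening, described as "safety-driven deterioration requiring urgent escalation of antiparkinsonian therapy", hospitalization for motor complications, or recurrent injurious falls;
- "Inability to continue due to poor adherence, frequent missed visits, or loss to follow-up", with two consecutive missed follow-up visits as the example;
- any other circumstance the study team judges unsuitable.

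The section keeps the reason for withdrawal and protects access to routine care. It does not mention later outcome visits.

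Table 1 ("Schedule of enrollment, interventions, and assessments") lists MADRS at screening, baseline, and Weeks 6, 8, 12 and 24. It shows no visit between baseline and Week 6 and no early-termination visit.

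Section 2.10 defines the ITT population as "all randomized participants analyzed according to the group to which they were assigned, regardless of adherence". On missing data it says: "Missing values will be assumed to be missing at random (MAR) within the MMRM framework". Multiple imputation and pattern-mixture models are planned as sensitivity analyses. Baseline MADRS enters the MMRM as a covariate.

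Three other sections bear on the point. Section 2.9 requires the intervention to stop at once after a serious adverse event. Section 2.6 keeps an unblinded participant's data in the primary analysis but names only safety follow-up for that participant. Section 2.7.2 says of antidepressants that "clinically indicated adjustments will be permitted for safety reasons or symptom worsening", and it also allows necessary antiparkinsonian dose changes with documentation.

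**The concern.** Stopping treatment and leaving the study are different events. An ITT analysis needs the second to be rare, because it compares groups as randomized whatever treatment was received. Section 2.3.3 treats the two as one. A site could reasonably read it as ending the Week 6 assessment along with the acupuncture.

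The schedule makes this matter more than usual. An MMRM normally draws on earlier post-baseline scores to support its missing-data assumption. Here the first post-baseline MADRS is the primary endpoint itself, so a participant who leaves before Week 6 has no such score to draw on.

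Some grounds may also relate to outcome or arm. Motor worsening can go with mood. Only the acupuncture arm has sessions to miss before Week 6 (18 of them, section 2.7.1), so the adherence ground can act differently by arm. Loss of worsening controls would pull the estimate towards no effect. Loss of poorly responding acupuncture participants would inflate it.

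**Working it through.** **Step 1. Which grounds can cost a Week 6 score?** Set section 2.3.3 against Table 1.

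| Ground | Can it act before Week 6 on the planned schedule? |
|---|---|
| Serious adverse event or serious illness | Yes, at the investigator's discretion |
| Urgent motor escalation, hospitalization, injurious falls | Yes |
| Inability to continue because of poor adherence | Yes; sessions exist only in the acupuncture arm |
| Study team judgement | Yes |
| MADRS rise above 50% | No; the first scheduled post-baseline MADRS is Week 6 |
| Suicide risk on C-SSRS | No; the first scheduled post-baseline C-SSRS is Week 6, when MADRS is also taken |
| Two consecutive missed follow-up visits | No; the follow-up visits come after Week 6 |

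**Step 2. What does such a participant contribute?** With no later assessment there is no post-baseline MADRS. Baseline is a covariate, so the participant supplies no response to the MMRM.

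**Step 3. The plan's own allowance for loss.** Section 2.4 inflates 35 completers for 20% dropout: 35 / 0.80 = 43.75, rounded up to 44 per group. This step reproduces. The implied loss is 0.20 × 44 = 8.8, about 9 per arm. How the 35 was obtained is a separate question and is not used here.

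**Step 4. Size of a possible shift.** Inputs from section 2.4: 44 per arm, SD 6.0, planned difference 2.4. Assumed: the number lost, *k*, and their mean deficit against the full arm mean, *d*, not explained by the baseline covariates. Removing *k* such participants moves the arm mean by *k* × *d* / (44 − *k*). The standard error of the difference is 6 × √(1/44 + 1/(44 − *k*)).

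Loss in one arm only:

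| *k* | Shift, *d* = 3 | Shift, *d* = 6 | *d* = 6 as share of 2.4 | SE | *d* = 6 in SEs |
|---|---|---|---|---|---|
| 1 | 3/43 = 0.07 | 6/43 = 0.14 | 6% | 1.287 | 0.11 |
| 2 | 6/42 = 0.14 | 12/42 = 0.29 | 12% | 1.294 | 0.22 |
| 4 | 12/40 = 0.30 | 24/40 = 0.60 | 25% | 1.311 | 0.46 |

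Loss in both arms, *d* = 6, 3 in one and 1 in the other: 18/41 − 6/43 = 0.439 − 0.140 = 0.30. Equal *k* and equal *d* in both arms: 0.

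**The case against.** The strongest reply is that this is a condensed article. Section 2.3.3 does not say that assessment stops, section 2.11 says the full protocol is available on request, and retrieval of data after withdrawal may be set out there. This stands in part: a reader might infer that sites are told not to collect Week 6 scores, and no section says so. But the article states a rule, withdrawal from the study, and no section assures a score after it. If the full protocol does assure one, the article's wording misstates it.

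Second, the document partly separates treatment from study elsewhere. Section 2.9 stops the intervention after a serious adverse event, section 2.6 keeps unblinded participants' data, and section 2.7.2 allows medication changes, so many worsening participants can be treated and kept. This narrows the problem. None of these provisions promises a Week 6 MADRS to someone withdrawn under 2.3.3.

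Third, a reader might infer that nothing observed after randomization bears on the loss. That is too strong. Adverse events, concomitant medication, attendance logs and withdrawal reasons are all recorded. They could inform the multiple imputation and pattern-mixture analyses. They are not in the stated primary model, and they do not replace the score.

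Fourth, a reader might infer that every missed session, MADRS rise or suicide-risk finding removes a Week 6 value. The text does not support this. The adherence ground requires inability to continue, section 2.12 attaches no withdrawal to falling below 80% of sessions, and the other two triggers are first scheduled at Week 6.

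Finally, the shifts are small for one or two losses, and neither input comes from the documents. That is correct and limits the weight of the point.

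**Conclusion.** The point holds as a wording gap with a real consequence. Followed as written, section 2.3.3 can lose primary-outcome data that the ITT definition in section 2.10 calls for, and it leaves the primary model's missing-at-random assumption resting on baseline covariates for those participants.

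The likely size is modest: 0.07 to 0.60 points in the one-arm illustration, at most about a quarter of the planned difference and under half a standard error. The top of that range needs four losses in one arm, none in the other, each a full SD worse than the arm mean. A reader might infer that the rule biases the trial in favour of acupuncture. The documents do not support that, because loss of worsening controls acts the other way and balanced loss cancels. The case for change rests on low cost and on timing: an analysis plan can model an uncollected Week 6 score but cannot recover it.

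**What to change.** Replace the opening rule of section 2.3.3 with:

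> Participants meeting a criterion will discontinue study acupuncture where applicable (immediately for an SAE, as in 2.9; otherwise under the existing criteria and investigator discretion). Unless consent is withdrawn, contact is lost, or assessment is clinically unsafe, participants in both arms remain in the study and attend the scheduled Week 6, 8, 12 and 24 assessments, including MADRS and MDS-UPDRS III, and these data are included in the ITT analysis.

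In section 2.6, widen the follow-up named for unblinded participants from safety alone to scheduled outcome and safety follow-up.

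The clinical thresholds, the investigator's discretion and the medication rules in section 2.7.2 stay as they are. No visit is added. Staff keep planned visits for the few who stop treatment: about 9 per arm if the assumed 20% dropout occurs, and fewer once lost contact and withdrawn consent, which wording cannot repair, are set aside. The 20% is a planning assumption, not a ceiling.
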